#### Body image

Three instruments were used to assess dimensions of body image i.e., the perception of one’s body weight status [37], Body Dissatisfaction subscale and Body Importance subscale extracted from the Body Image and Body Change Inventory [38], and the Body Image Scale. The questionnaire used had been shown to be valid and reliable when used in studies that involve adolescents [38]. Perception of current weight status will be assessed by using parameters adapted and modified from Simko et al. [37]. Parameters will be ranked 1 (very thin) to 5 (obesity). Thereafter, adolescents’ perceptions of their current weight status will be compared to their actual weight status. Body image will be estimated based on the following calculation:$$ \mathrm{Body}\ \mathrm{Image} = \mathrm{Perceived}\ \mathrm{body}\ \mathrm{size} - \mathrm{Actual}\ \mathrm{body}\ \mathrm{size} $$

A ‘correct-estimator’ will correspond to a score of 0; an ‘under-estimator’ will be identified when the score is < 0; and an ‘over-estimator’ referred to subjects with a score > 0.

Body Dissatisfaction subscale consisted of 10 items with five response categories, ranging from 1 (extremely satisfied) to 5 (extremely dissatisfied). Similarly, Body Importance subscale consisted of 10 items with five response categories, ranging from 1 (extremely important) to 5 (not important at all). Body Image Scale will also be used to assess adolescents’ satisfaction with their own body sizes. Nine body figures will be consulted, ranging from 1 (the thinness body size) to 9 (the biggest body size). Participants’ actual body size, perceived ideal body size and healthy body size will be identified. The discrepancy score will be calculated as follows:$$ \mathrm{Satisfaction} = \mathrm{Perceived}\ \mathrm{current}\ \mathrm{body}\ \mathrm{size} - \mathrm{Perceived}\ \mathrm{ideal}\ \mathrm{body}\ \mathrm{size} $$

‘Satisfied with body size’ will correspond to a score of 0. ‘Dissatisfied with a desire to be larger’ will be implied by a score < 0, while ‘dissatisfied with a desire to be thinner’ will be implied by a score > 0.

#### Health-related quality of life (HRQoL)

Pediatric Quality of Life Inventory 4.0 (PedsQL™4.0) [39] will be used to assess health-related quality of life (HRQoL) among the adolescents using 23 items. Adolescents were asked to recall health-related problems experienced in the past month and rank the frequency, with 0 being never had a problem, and 4 being almost always had a problem. Scores of all items were plotted on a 0–100 point scale (0 = 100, 1 = 75, 2 = 50, 3 = 25, 4 = 0). Higher total PedsQL™ scores corresponds to better HRQoL.

PedsQL™ will be interpreted based on an ordered scale. The lower orders scale had four dimensions [40]: Physical Functioning (eight items), Emotional Functioning (five items), Social Functioning (five items) and School Functioning (five items). These four dimensions will be combined to derive a higher order scale comprising two dimensions: Physical Health (physical functioning subscale) and Psychosocial Health (emotional, social and school functioning subscales). PedsQL™ 4.0 had been shown to be valid and reliable to assess HRQoL in Malaysian adolescents [41].

#### Self-esteem

Rosenberg Self-esteem Scale (RSES) [42] will be used to measure adolescents’ self-esteem. The scale consisted of 10 items. Assessment assumes 1 as “strongly agree” and 4 as “strongly disagree”. RSES had been shown to be reliable and valid when used in studies involving adolescent groups [43, 44].

#### Pubertal stage

Pubertal Development Scale (PDS) [45] will be used to detect puberty in adolescents. Five characteristics will be assessed: spurt in height; pubic hair; skin changes; facial hair growth and voice change in males; and breast development and menarche in females. Except for menarche, to which a dichotomous response scale (‘yes’ or ‘no’) will be used, answers regarding puberty were provided by using a four-point Likert scale whereby 1 signifies no development, while 4 indicates that development was complete. Based on the given scores, the adolescents will be categorized into five pubertal groups: pre-pubertal, early pubertal, mid-pubertal, late pubertal and post-pubertal.

#### Eating behaviour

Two questionnaires will be used to assess adolescents’ eating behaviours: Three-Factor Eating Questionnaire-R18 (TFEQ-R18) [46, 47] and Eating Behaviour Questionnaire (EBQ) [48]. TFEQ-R18 will be used to determine current dietary practices. It measured three different aspects of eating behaviour: Cognitive restraint (tendency to constantly and consciously restrict food intake instead of using physiological cues, hunger and satiety as regulators of food intake), uncontrolled eating (tendency to overeat, with a feeling of losing control), and emotional eating (tendency to eat in response to negative emotions) [49]. Overall, TFEQ-R18 consisted of 18 items will be answered using a 4-point response scale whereby 1 is “definitely true” and 4 is “definitely false”.

EBQ will rather be used to assess main meal consumption and snacking behaviour, as well as family meals, eating outside and favouring take-away food. EBQ comprised of 11 items with 8 response categories ranging from 0 (0 day) to 7 (7 days). Adolescents will responded by stating the frequency of food intake in the past seven days.

#### Dietary intake

Food consumption, energy and nutrient intake will be assessed via 1-day dietary recall. Adolescents will be interviewed to determine the type and amount of foods and beverages they consumed on daily bases, as well as the food and beverage brands they preferred and the food preparation methods they used. Household measurements will be prepared to assist adolescents in estimating the quantity of food and beverages they consumed. The Nutritionist Pro™ Diet Analysis software will be used to assess energy, macronutrients and sugar intake. The software will also be used to estimate daily serving size of rice, bread, cereals, cereal products, vegetables, fruits, fish, poultry, meat, legumes, milk and dairy products.

#### Physical activity

Energy expenditure through physical activity will be assessed using one-day physical activity recall. Adolescents will be asked to recall all the activities they performed, including sitting, standing and walking, every 15 min during a 24-h period. Assessment of physical activity will be conducted on the same day of dietary recall. Every activity will be assigned an MET value based on the Compendium of Physical Activities (1 MET = 3.5 ml of oxygen/ kg body weight/ min or resting metabolic rate) [50, 51]. Energy expenditure during every activity will be calculated by multiplying the value of MET, the duration of the activity (hour) and body weight (kg) [50]. Total daily energy expenditure (TDEE) will be calculated by determining the sum of energy expenditure per activity per day. The physical activity level (PAL) of the participants will be calculated by dividing TDEE by the basal metabolic rate (BMR) [52], and will be classified into four categories: Sedentary (PAL < 1.40), light (PAL = 1.40–1.69), moderate (PAL = 1.70–1.99) and vigorous (PAL = 2.00–2.40) [52].

#### Knowledge, attitude and practice of healthy lifestyle

A Knowledge, Attitude and Practice of EPaL Lifestyle Questionnaire (KAP-ELQ) was developed prior to data collection to measure the construct of knowledge, attitude and practice in relation to healthy eating, physical activity and body image among adolescents. The instrument consisted of items adapted from standard questionnaires, literature reviews and text books. KAP-ELQ comprised 32 multiple-choice questions pertaining to knowledge. Additionally, 24 items with six response categories, ranging from 1 (strongly disagree) to 6 (strongly agree), will determine adolescents’ attitude towards a healthy lifestyle. Moreover, practice of a healthy lifestyle will be assessed by answering 35 items, 13 of which had five response categories whereby 1 meant “every day” and 5 meant “never”. The other 22 items also had five response categories; however, 1 implied “very often”, while 5 implied “never”. The items had been reviewed for suitability, relevance and accuracy by an expert panel comprising of nutritionists and health educators. Based on the feedback and recommendations by the expert panel, the items were either retained unchanged, revised or removed.

### Data analysis

Data will be analysed by using version 21 of the IBM SPSS Statistical software (IBM SPSS Statistics, Inc., Chicago, IL, USA). Depending on the distribution of the variable of interest, descriptive statistics of continuous data will be presented by using the mean and standard deviation, and the median and the inter-quartile range. Categorical data will be presented as frequencies and percentages. *T*-test will be used to detect differences between groups for continuous variables, while chi-square will be used to investigate possible correlations between categorical variables. The repeated measures analysis of variance (ANOVA) will be used to detect significant differences within the groups. The evaluation of the intervention will be based on an intention-to-treat analysis. Differences with *p*-values < 0.05 were considered significant.

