Healthy Lifestyle in Children (HELIC) [23], Healthy Kids Programme [24], Body Image Education Package [25] and the Malaysian Childhood Obesity Treatment Trial (MASCOT) [26] are a few of many school-based interventions that had been implemented in Malaysia. However, most of these interventions have rather been stand-alone programmes in the sense that they focused either on the prevention of obesity or the prevention of disordered eating. As far as our knowledge goes, Malaysia has not seen a comprehensive intervention programme that promotes all three components of a healthy life: healthy eating, active lifestyle and positive body image.

‘Eat Right, Be Positive About Your Body and Live Actively’ (EPaL) is an integrated health education intervention, which developed to prevent overweight and disordered eating among Malaysian adolescents. This intervention was formulated with the understanding that obesity, disordered eating, and extreme weight loss practices were strongly correlated and shared the same risk factors. Hence, it delivered a coherent message while tackling a broad spectrum of eating- and weight-related health issues. Unlike Healthy Buddies, EPaL did not use a one-to-one approach [22], but rather involved training a group of adolescents to become peer educators who then led others to fully implement the intervention. It differed from MABIC as it stipulated that the trainees be adolescents rather than educators or health care providers, such as tutors, clinical psychologists and nurses [20].

This paper describes the protocol for an integrated health education intervention namely ‘Eat Right, Be Positive About Your Body and Live Actively’ (EPaL), a primary prevention which aimed to promote healthy lifestyle, which including healthy eating, positive body image and active lifestyle, in preventing overweight and disordered eating among first and second year secondary school adolescents. In the present work, adolescents were used to ascertain whether or not EPaL could serve as an effective tool to promote health in Malaysian adolescents and reduce the incidence of overweight and disordered eating. The intervention was developed by taking consideration on risk factors and cultural background of Malaysian population, which might be different from other countries. The risk factors of interest were determined beforehand by carrying out a wide survey amongst secondary school adolescents throughout Malaysia.

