### Sample size calculation

The sample size calculation was based on the differences between groups (overweight and obese; and non-overweight and non-obese) in the proportion of having disordered eating. The value was taken from the outcome of needs assessment study, which was conducted involving 9677 adolescents aged 12–19 years throughout Malaysia. Based on the study, the proportion of overweight and obese adolescents who were having disordered eating was 40.3 %, whereas the proportion of non-overweight and non-obese adolescents who were having disordered eating was 27.9 %. Assuming a power of 80 % and a level of significance of 5 %, we needed 234 participants for each intervention and comparison groups, respectively. The effect size for proportions was estimated by the differences in the arcsine transformations of the respective proportions. The medium effect size of 25.4 % was obtained.

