#### Socio-demographic characteristics

Adolescents will answer questionnaires regarding their socio-demographic backgrounds, including gender, ethnicity, age, date of birth, number of family members living together, number of siblings, academic achievements and parents’ background (educational level, occupation and monthly income).

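### No stated between-group analysis uses the baseline values, so with one school per arm a stable school difference can be read as an EPaL effect

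*Protocol article*

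**What the plan says.** The Data analysis section assigns each method a job. For comparing the arms, the t-test "will be used to detect differences between groups for continuous variables, while chi-square will be used to investigate possible correlations between categorical variables". Repeated-measures ANOVA "will be used to detect significant differences within the groups". The section adds that evaluation is by intention to treat and that p < 0.05 is significant. It names no change score, group-by-time term, regression model or covariate.

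Under Study design, one school receives EPaL and another is the comparison. Under Setting, recruitment and participants, both schools come from a draw and the intervention school is chosen at random. The Discussion acknowledges that randomisation went no further than the schools.

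Under Measurements, all participants in both schools are assessed at baseline, after the last session and 3 months later. Covariates are collected as well: gender and age, "academic achievements and parents’ background (educational level, occupation and monthly income"), and pubertal stage, for which "the adolescents will be categorized into five pubertal groups". The Data analysis section gives none of these a role.

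The aims are worded in two ways. One part of the Background hopes to "reduce the incidence of overweight and disordered eating"; another speaks of changing prevalence. Eligibility does not exclude students who already have either condition.

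**The concern.** A draw that decides which of two schools gets EPaL does not balance the students, because there is no averaging over schools. The two intakes may differ in BMI, eating attitudes or maturity before the first session. An unadjusted comparison of later values carries that difference into the estimated effect in full, and nothing in the test output reveals it. The baseline data that could correct much of this will be available for every participant.

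At stake is the claim that EPaL works. A significant t-test or chi-square at follow-up could reflect nothing more than the intake of the two schools. A difference in the other direction could hide a real benefit. A within-group ANOVA in each school does not help, since a change in one school says nothing about whether it exceeds the change in the other.

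**Working it through.** **Inputs from the protocol.** 234 per group, 80% power, 5% significance, 40.3% versus 27.9% (Sample size calculation). Sidedness is not stated; two-sided is assumed.

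**Inputs assumed.** The documents give no between-school figures, so the school difference d (in SD units), the prevalence gap and the baseline-to-follow-up correlation r are shown as ranges.

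**The plan's own figure.** The article says "we needed 234 participants for each intervention and comparison groups, respectively". The pooled two-proportion formula for 40.3% versus 27.9% gives 229 per group and the arcsine formula gives 228; power at 234 is 81%. The stated size reproduces to within 3% and is used below.

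**Step 1: t-test on follow-up values, no EPaL effect.** The standard error of the mean difference is √(2/234) = 0.0925 SD. Rejection = Φ(d/0.0925 − 1.96) + Φ(−d/0.0925 − 1.96).

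| d (SD) | d/0.0925 | Rejection |
|---|---|---|
| 0 | 0 | 5% |
| 0.1 | 1.08 | 19% |
| 0.2 | 2.16 | 58% |
| 0.3 | 3.24 | 90% |

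**Step 2: chi-square on follow-up prevalence, no EPaL effect.** For an assumed stable 28% versus 34%, the pooled proportion is 0.31 and the standard error is √(0.31 × 0.69 × 2/234) = 0.0428. Then z = 0.06/0.0428 = 1.40, and rejection is 29%. Other assumed gaps: 27.9% versus 32.9% gives 22%, and 27.9% versus 35.9% gives 46%.

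**Step 3: what the alternatives do with the same stable difference.** In a contrast of change from baseline, d cancels. In simulation (3,000 runs per setting, r = 0.5 to 0.8, d = 0.1 to 0.3) rejection was 4.4% to 5.6%.

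ANCOVA removes only the part r·d and leaves d(1 − r), with standard error √((1 − r²) × 2/234). At d = 0.2 and r = 0.7 the residual is 0.06, the standard error √(0.51 × 2/234) = 0.0660, the ratio 0.91 and the rejection 15%. At d = 0.2 it is 24% for r = 0.5 and 11% for r = 0.8. ANCOVA therefore reduces the problem without removing it.

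**Step 4: precision.** For a continuous outcome, ANCOVA leaves 1 − r² of the variance, equivalent to 1/(1 − r²) times the sample.

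| Assumed r | 1 − r² | Equivalent sample |
|---|---|---|
| 0.3 | 0.91 | 1.1 times |
| 0.5 | 0.75 | 1.3 times |
| 0.7 | 0.51 | 2.0 times |

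A high r cannot be presumed for the one-day dietary and activity recalls, and this rule does not carry over to logistic regression.

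**The case against.** The strongest reply is that the article never says the t-test is run on follow-up values. On change scores a stable school difference would drop out. This stands. A reader might infer that any pre-existing difference is bound to be counted as an EPaL effect, and the text does not support that. It supports something narrower: no stated contrast uses baseline, and the wording permits the vulnerable analysis.

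A second reply is that the schools were drawn under common criteria (coeducational, multiracial, non-residential, non-religious) and the intervention school was chosen at random, so over repeated draws the contrast is not systematically biased. That is fair. The rejection rates above are conditional on a given school difference, and the documents give no value for it. But only one draw is made, and its difference is fixed for the whole trial. The Discussion discloses the design limit, which does not make up for leaving measured imbalance unused.

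A third reply is that a condensed article may leave covariate lists to a fuller plan. This stands for the list itself. It does not stand for the tests, which the article names.

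Two further inferences should be resisted. The wish to reduce incidence does not make a prevalence comparison wrong, because the Background also states a prevalence aim. And choosing peer educators partly on academic performance in the intervention school does not by itself change that school's intake, so it gives no special reason to adjust for academic achievement.

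**Conclusion.** The point holds in this form: the stated between-group tests are unadjusted, the repeated-measures analysis is confined to change within groups, and the baseline values collected in both schools enter no stated comparison. If the tests are applied to later values, a stable school difference as small as 0.1 SD raises the false-positive rate from 5% to 19%, and 0.2 SD raises it to 58%. These sizes rest on assumed differences that persist unchanged, on 234 students per arm and on two-sided 5% tests.

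The remedy has limits. A change contrast removes a stable difference but not differing trends between the schools. ANCOVA removes only part of a stable difference. Neither separates school from intervention, because one school per arm leaves the variation between schools inestimable. The precision gain depends on the outcome and should not be promised in general. The change should be made: it bears on the effectiveness claim and needs no new data, though it does not cure the design.

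**What to change.** In Data analysis:

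- **Continuous outcomes.** Make the evaluation of EPaL a group-by-time contrast (difference between schools in change from baseline), from a mixed or repeated-measures model with group as a between-subject factor. Report baseline-adjusted ANCOVA as a sensitivity analysis.
- **Binary outcomes.** Use logistic regression adjusted for baseline status, or a longitudinal logistic model with a group-by-time term.
- **Covariates.** Pre-list a short set already collected, such as sex, Form or age, and pubertal stage.
- **t-test and chi-square.** Keep them for the baseline table.
- **Incidence.** As a supplement, report new overweight and new disordered eating among students free of that condition at baseline, noting the smaller sample.
- **Limits.** State that ANCOVA reduces but does not remove a stable school difference (about 15% rejection at 0.2 SD with r = 0.7, against about 5% for change), and that no adjustment separates school from intervention with one school per arm.

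The cost is analysis wording and syntax. Every variable needed is already collected.

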#### Stages of change

According to the Transtheoretical Model, five stages of change will be identified: Pre-contemplation, contemplation, preparation, action and maintenance for healthy diet [32], breakfast, food portion size, screen-viewing time (television/ video/ DVD) [33] and physical activity [34]. This model will be used to determine adolescents’ adherence to a healthy lifestyle before and after the implementation of the intervention. This will provided a clear view of the progress that the participants made in terms of adopting and maintaining health behaviours [35].

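### Chi-square on the five ordered stages of change ignores their order and loses power against a consistent forward shift

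*Protocol article*

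**What the plan says.** The Data analysis section of the protocol article gives the t-test to continuous variables and states that "chi-square will be used to investigate possible correlations between categorical variables". Repeated measures ANOVA is named for differences within groups. Categorical data are also to be described by frequencies and percentages. No rank, trend or ordinal method appears.

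The Stages of change section says that "five stages of change will be identified: Pre-contemplation, contemplation, preparation, action and maintenance", and applies this to healthy diet, breakfast, food portion size, screen-viewing time and physical activity. It gives the purpose twice: "This model will be used to determine adolescents’ adherence to a healthy lifestyle before and after the implementation of the intervention", and the result "will provided a clear view of the progress that the participants made in terms of adopting and maintaining health behaviours".

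The Sample size calculation section sets 234 participants per group for a binary outcome, disordered eating ("Assuming a power of 80 % and a level of significance of 5" per cent). No distribution, expected shift or power is given for stages of change.

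**The concern.** Progress from pre-contemplation to maintenance is a directional question. Pearson chi-square on a table of two groups by five stages asks only whether the two distributions differ in any way. It has (2 − 1) × (5 − 1) = 4 degrees of freedom and gives the same value if the columns are reordered. Two things follow.

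- A real, consistent movement towards later stages is more likely to be missed, because the test spreads its sensitivity over patterns nobody is looking for.
- A significant result need not mean progress. Pupils moving backwards, or towards both extremes, can produce it too.

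The test also looks at one time point and cannot take the baseline stage into account. The comparison is between two schools, with no randomisation of individual pupils.

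**Working it through.** **The plan's own figure.** Inputs from the Sample size calculation section: 40.3 %, 27.9 %, 80 % power, 5 % significance (sidedness not stated, taken as two-sided).

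- h = 2·asin(√0.403) − 2·asin(√0.279) = 0.263
- n = 2·((1.960 + 0.842)/h)² = 2 × 7.849 / 0.263² ≈ 228 per group; the pooled two-proportion formula gives 229

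The stated 234 is within 3 % of both, and power at 234 is about 81 %. This outcome is binary, so chi-square has 1 degree of freedom and loses nothing. The 234 is used below only as the group size.

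**Analytic check.** If an order-using test on 1 degree of freedom captures the whole effect, its noncentrality at 80 % power is (1.960 + 0.842)² = 7.849. Putting the noncentrality for each reference power into a noncentral chi-square on 4 degrees of freedom gives:

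| Power on 1 df | Power on 4 df | Loss (points) |
|---|---|---|
| 50 % | 30.8 % | 19 |
| 70 % | 48.2 % | 22 |
| 80 % | 59.5 % | 20.5 |
| 90 % | 74.0 % | 16 |
| 95 % | 83.7 % | 11 |

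**Simulation.** 234 per group, independent pupils, two-sided 5 %, one common odds ratio towards later stages. The stage distributions in the comparison group are assumptions, since the article gives none.

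| Assumed stages (%) | Odds ratio | Chi-square | Wilcoxon | Loss (points) |
|---|---|---|---|---|
| 20/25/25/20/10 | 1.4 | 33 % | 53 % | 20 |
| 20/25/25/20/10 | 1.5 | 48 % | 69 % | 21 |
| 20/25/25/20/10 | 1.6 | 61 % | 82 % | 21 |
| 20/20/20/20/20 | 1.35 | 26.7 % | 45.0 % | 18 |
| 20/20/20/20/20 | 1.49 | 46.8 % | 68.7 % | 22 |
| 20/20/20/20/20 | 1.82 | 85.1 % | 95.7 % | 11 |
| 35/25/20/12/8 | 1.49 | 45.9 % | 67.8 % | 22 |
| 35/25/20/12/8 | 1.82 | 84.2 % | 95.2 % | 11 |
| 30/10/20/10/30 | 1.49 | 45.4 % | 67.0 % | 22 |
| 30/10/20/10/30 | 1.82 | 83.3 % | 95.0 % | 12 |

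The last seven rows come from log odds ratios of 0.30, 0.40 and 0.60. The linear-by-linear trend test gives almost the same power as Wilcoxon. Repeat runs of the first three rows agree to within about two points. The range is therefore roughly 10 to 22 points.

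**Type I error.** With no difference between groups, chi-square rejects in 5.2 % of runs and both order-using tests in 5.1 %. All three are valid.

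**A case where the ranking reverses.** Start from equal stages and move 10 percentage points from preparation to action only. Chi-square then has 82.6 % power and the trend test 11.3 %.

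**The case against.** **The assignment is inferred.** The Data analysis section does not mention stages of change, and a condensed article may leave outcome-by-outcome tests to a fuller plan. This is fair as a caution. But the sentence on categorical variables is a general rule, and the article offers no other between-group test for a categorical outcome.

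**Chi-square is not wrong.** This stands. Its error rate is correct, and the planned frequencies and percentages let a reader see the direction. They do not supply a test or an estimate of it.

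**The loss is not a fixed number.** This stands too. A reader might infer that the plan simply loses about 20 points. The documents give no stage distribution or effect from which that could be claimed, and the reversal above shows that chi-square can win when movement is confined to one adjacent pair of stages.

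**Other ordered categories.** A reader might wish to treat weight status and PAL category the same way. The documents do not support this.

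- The statement about progress belongs to stages of change alone.
- Weight status runs from severe thinness to obesity with the healthy category in the middle, so benefit can mean moving inward from both ends. Take overweight at 14.2 % and obesity at 10.1 % (Background section), assume thinness at 6 to 10 %, and cut all three by an assumed 40 %. Chi-square then has about 74 to 81 % power and a rank test about 29 to 46 %.
- PAL ("will be classified into four categories") is cut from a continuous ratio, and the planned t-test already covers continuous variables.

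**Baseline adjustment.** Its absence applies equally to the planned t-test, so it is not peculiar to chi-square. It is a further gain from the proposed model, not the core of this point.

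**Conclusion.** The point holds for stages of change, as a minor improvement in efficiency and interpretation. The named test ignores the order of the five stages and cannot show the progress they are meant to show.

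Under proportional odds, with independent pupils, 234 per group and assumed stage distributions, the cost is roughly 10 to 22 percentage points of power. It shrinks when power is already high, and it reverses when movement is confined to one adjacent pair of stages. The independence assumption is optimistic with one school per arm, and neither kind of test cures that.

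A reader might infer that the trial's stated 80 % power is undermined. It is not: that figure is for binary disordered eating, where chi-square has 1 degree of freedom.

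**What to change.** In the Data analysis section, add a rule for stages of change only. At post-intervention and at the 3-month follow-up, compare the groups for each behaviour with a proportional-odds model containing group and baseline stage. Report the common odds ratio with its 95 % confidence interval, alongside the planned frequencies and percentages. If a simple test is preferred, use a Wilcoxon or linear-by-linear trend test.

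Keep chi-square for unordered variables such as ethnicity. Do not apply the change to weight-status category, and analyse PAL as the continuous ratio.

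The cost is a change of analysis wording, with standard software and no new data. The downside is small: the method relies on a roughly consistent shift and has less power if movement is confined to one adjacent pair of stages. The tabulated frequencies would show such a pattern.
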